#### Outcomes and Analysis

The five elements of the RE-AIM framework will be used as an overarching construct for reporting outcomes for this study (Figure 2).

#### *Reach*

The primary implementation outcome (the percentage of consented participants successfully transitioned to PSM) will be calculated using the following denominators 1) all patients receiving warfarin; 2) all patients invited to participate in the study and attempt PSM including those who decline participation; and 3) all participants who provide informed consent and attempt transitioning to PSM. Successful transition to PSM will be defined as completing 6-months of PSM. The timing of PSM transition failures during the 6-month follow-up period will be recorded. Reasons patients refuse to participate in PSM implementation activities and reasons patients failed to successfully transition to PSM during implementation efforts will be recorded and categorized.

Data for “reach” outcomes will be summarized using descriptive statistics. Differences in baseline characteristics between eligible patients who do and do not agree to participate in the PSM implementation phase and between those who do and do not successfully transition to PSM will be compared using the chi-squared test of association (categorical variables), Fisher’s

exact test (categorical variables that occurred infrequently) or Student's t-test (continuous variables). Two-sided p-values <0.05 will be considered statistically significant.

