## **Abstract**

**Introduction:** Warfarin is a narrow therapeutic index drug that requires frequent monitoring using the international normalized ratio (INR). Current clinic-based INR monitoring models lead to suboptimal warfarin management. Warfarin patient self-management (PSM) has consistently demonstrated superior efficacy compared to clinic-based management but is virtually unused in the US healthcare system. The objective of this study is to implement PSM in the US healthcare system using strategies developed to overcome previously identified barriers associated with PSM underutilization as well as potential PSM facilitators.

**Methods and analysis:** We aim to implement PSM with 150 adult patients at four sites using strategies developed to address barriers to PSM specific to the US healthcare system. Implementation strategies will be guided by the Consolidated Framework for Implementation Research and the Quality Implementation Framework supported by Rapid Cycle Research Methodology. A type III hybrid implementation-effectiveness study design will be used to assess PSM implementation strategy outcomes while also gathering information on PSM clinical outcomes centered on the five elements of the RE-AIM framework (Reach, Effectiveness, Adoption, Implementation, Maintenance). This study will be approved by the ethics boards at all participating sites.

**Discussion:** We plan to disseminate the results of this research program examining the feasibility of PSM in US anticoagulation management services in scientific journals and conferences, as well as making elements of the PSM implementation toolkit publicly and freely available.

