### *Effectiveness*

The following INR control outcomes will be compared between eligible participants who do and do not successfully transition to PSM during the 6-month follow-up period, 1) individual time in the therapeutic INR range (TTR) using linear interpolation; and 2) proportion of INRs resulting in a warfarin dose change. INR control outcomes will also be compared between the 6-month periods before and after PSM transition attempts (Figure 2).

Additional effectiveness outcome comparisons before and after PSM transition will include major bleeding and clinically relevant non-major bleeding events as defined by the International Society on Thrombosis and Haemostasis, thromboembolic events, and all-cause mortality. Thromboembolic events will include stroke, systemic embolism or venous thromboembolism documented by objective imaging. Bleeding and thromboembolic events will be confirmed by manual EHR review. For participants who successfully transition to PSM, AKT, ACT, and SF-36 scores will be compared before and after PSM transition.

Data analysis for "effectiveness" outcomes will consist of basic descriptive statistics. T-tests and the chi-squared test of association will be used to compare differences in continuous and categorical outcomes between patients who do and do not successfully transition to PSM during the 6-month PSM phase. Paired t-tests and McNemar's test will be used to compare differences between continuous and categorical outcomes before and after PSM transition, respectively. Two-sided P-values <0.05 will be considered statistically significant.

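### The protocol names Student's equal-variance t-test for groups whose sizes are not set by design; Welch's test would hold the stated 5% level at almost no cost (minor).

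*Protocol*

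**What the plan says.** Under Outcomes and Analysis, the Reach section plans tests of "Differences in baseline characteristics between eligible patients who do and do not agree to participate in the PSM implementation phase", and likewise between those who do and do not succeed with PSM. The named methods are the chi-squared test, Fisher's "exact test (categorical variables that occurred infrequently) or Student's t-test (continuous variables"). The threshold follows directly on the named test: Student's "t-test (continuous variables). Two-sided p-values <0.05 will be considered statistically significant". By its usual meaning Student's t-test is the pooled, equal-variance form, although the protocol does not write either of those words.

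Success is an outcome: "Successful transition to PSM will be defined as completing 6-months of PSM". The enrolment target is given in the Abstract: "We aim to implement PSM with 150 adult patients at four sites".

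The Effectiveness section compares time in therapeutic range (TTR) and the proportion of INRs leading to a dose change across the same success split: "T-tests and the chi-squared test of association will be used to compare differences in continuous and categorical outcomes between patients who do and do not" succeed. The form of t-test is not named there. The two-sided 0.05 threshold applies again.

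**The concern.** The pooled test estimates one common variance, weighted towards the larger group. If the smaller group is the more variable one, the standard error comes out too small and the test rejects too often. If the smaller group is the less variable one, the standard error is too large and the test rejects too rarely.

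Nothing in the design balances these groups. The success split depends on who completes six months, and the participation split depends on who consents. Participants must already be self-testing, have had more than 9 months of warfarin, and pass clinician screening and a readiness judgement. A smaller non-success group is therefore a reasonable expectation, although no rate is stated.

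What is at stake is the meaning of a p-value below 0.05 when describing who agrees, who succeeds and, if the pooled form is used there too, how INR control differs.

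**Working it through.** **Inputs.** From the protocol: N = 150, taken as success plus non-success; two-sided alpha 0.05; Student's t-test. Assumed, because the protocol gives neither: the split n1 (success) / n2 (non-success), and r = SD(non-success)/SD(success). The protocol has no power or error-rate figure of its own to reproduce.

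**Large-sample formula.** With the success SD set to 1:

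- Variance the pooled test uses: V = [(n1 + n2·r²)/(n1 + n2)]·(1/n1 + 1/n2)
- True variance of the difference in means: T = 1/n1 + r²/n2
- Actual level = 2·[1 − Φ(1.96·k)], where k² = V/T

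**At 120/30:**

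- r = 1: V = T = 0.0417, k = 1, level 5.0%
- r = 1.25: V = 0.0464, T = 0.0604, k = 0.876, level 8.6%
- r = 1.5: V = 0.0521, T = 0.0833, k = 0.791, level 12.1%
- r = 2: V = 0.0667, T = 0.1417, k = 0.686, level 17.9%
- r = 0.67: V = 0.0371, T = 0.0233, k = 1.262, level 1.3%

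**Simulation.** Normal data, equal means, 100,000 replicates per cell. Actual level of the pooled test:

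| Success/non-success | r = 0.67 | r = 1 | r = 1.25 | r = 1.5 | r = 2 |
|---|---|---|---|---|---|
| 135/15 | 0.7% | 5.0% | 9.8% | 15.2% | 24.9% |
| 120/30 | 1.4% | 5.0% | 8.6% | 12.2% | 17.9% |
| 105/45 | 2.3% | 5.0% | 7.4% | 9.6% | 12.6% |
| 90/60 | 3.4% | 5.0% | 6.2% | 7.0% | 8.4% |
| 75/75 | 5.2% | 5.1% | 5.0% | 5.0% | 5.1% |
| 50/100 | 8.5% | 5.0% | 3.5% | 2.6% | 1.7% |
| 30/120 | 12.1% | 5.1% | 2.6% | 1.4% | 0.4% |

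Welch's test gave 4.9% to 5.1% in every cell. Where both were run (r from 1 to 2, splits from 135/15 to 75/75), formula and simulation agree within 0.4 percentage points.

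**Agree versus decline.** Assume 150 agree. With 300 decliners the pooled level is 2.6% if the decliners' SD is 1.5 times larger, and 8.5% if it is 0.67 times as large. With 150 decliners it is 5.1% either way.

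**Could r exceed 1 for the Effectiveness outcomes?** Testing every 1 to 2 weeks over 26 weeks gives 26/2 = 13 to 26 INRs per completer. Suppose non-completers' INRs count only until PSM failure. Take an assumed mean dose-change proportion of 0.20 and a between-patient SD of 0.10 in both groups. The variance of one patient's observed proportion from m INRs is 0.01 + (0.20·0.80 − 0.01)/m:

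- m = 18: 0.01 + 0.15/18 = 0.0183
- m = 6: 0.01 + 0.15/6 = 0.0350, so r = √(0.0350/0.0183) = 1.38
- m = 12: 0.01 + 0.15/12 = 0.0225, so r = √(0.0225/0.0183) = 1.11

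Simulating these skewed proportions with 18 versus 6 INRs gives a pooled level of about 10% at 120/30 and 13% at 135/15. Welch gives about 5% and 6%. With 18 versus 12 INRs at 120/30, pooled is about 6% and Welch about 5%.

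**The case against.** A reader might infer that these comparisons will produce false positives well above 5%, and that the TTR comparison in particular is inflated. The protocol does not support that, for four reasons.

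- **Size and direction are unknown.** There is no expected success rate, no count of decliners and no SD. The smaller group could be the less variable one, which makes the test conservative, and imbalance alone does nothing. The levels of 18% and above need an SD ratio of 2, for which the protocol offers no basis.
- **The named test and the variance mechanism sit in different sections.** Student's form is fixed only for baseline characteristics. Shorter PSM follow-up cannot change the spread of age or of prior warfarin duration. The outcomes it could affect are under Effectiveness, where Welch's test already fits the wording.
- **The mechanism is itself conditional.** The Implementation (Fidelity) section censors its data at PSM failure. The Effectiveness section does not say whether non-completers' INRs stop there or run for six months.
- **Little depends on it.** These are nominal p-values in a feasibility study, and willingness to participate is also modelled by multivariable logistic regression.

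All four stand, and they limit the point to a conditional, minor one. A further objection, that the variance form is a detail for the statistical analysis plan, stands for Effectiveness. It does not stand for Reach, where the protocol names a test, and an analysis plan that follows the protocol would inherit it.

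**Conclusion.** The point holds as a minor, conditional improvement. The Reach section fixes a test whose 5% level depends on equal variances or equal group sizes, and the protocol gives no reason to expect either. Over the assumed splits and SD ratios the actual level runs from below 1% to about 25%, in a direction that cannot be known in advance. The assumptions are normal data, N = 150, and the splits and ratios shown.

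Greater spread among non-completers is plausible for the Effectiveness outcomes if their INRs are counted only to failure. No such mechanism is shown for the baseline variables. The primary implementation outcome does not use a t-test, so nothing here touches it.

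**What to change.** In the Reach section, replace Student's t-test with Welch's unequal-variance t-test. In the Effectiveness section, name Welch's test for the comparisons between those who do and do not succeed. The paired t-tests there need no change.

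This needs no new data and only a few words. If the SDs are in fact equal, Welch gives up a little power through fewer degrees of freedom, with df = (1/n1 + 1/n2)² / [(1/n1)²/(n1 − 1) + (1/n2)²/(n2 − 1)]. At 120/30 this is about 45, so the critical value is 2.02 against 1.98 for the pooled test. At 135/15 it is about 17, with a critical value of 2.11. The loss is therefore negligible unless the smaller group is very small. With about 15 skewed observations Welch can itself run slightly high (about 6%), still much closer to 5% than the pooled test.

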### *Effectiveness*

The following INR control outcomes will be compared between eligible participants who do and do not successfully transition to PSM during the 6-month follow-up period, 1) individual time in the therapeutic INR range (TTR) using linear interpolation; and 2) proportion of INRs resulting in a warfarin dose change. INR control outcomes will also be compared between the 6-month periods before and after PSM transition attempts (Figure 2).

Additional effectiveness outcome comparisons before and after PSM transition will include major bleeding and clinically relevant non-major bleeding events as defined by the International Society on Thrombosis and Haemostasis, thromboembolic events, and all-cause mortality. Thromboembolic events will include stroke, systemic embolism or venous thromboembolism documented by objective imaging. Bleeding and thromboembolic events will be confirmed by manual EHR review. For participants who successfully transition to PSM, AKT, ACT, and SF-36 scores will be compared before and after PSM transition.

Data analysis for "effectiveness" outcomes will consist of basic descriptive statistics. T-tests and the chi-squared test of association will be used to compare differences in continuous and categorical outcomes between patients who do and do not successfully transition to PSM during the 6-month PSM phase. Paired t-tests and McNemar's test will be used to compare differences between continuous and categorical outcomes before and after PSM transition, respectively. Two-sided P-values <0.05 will be considered statistically significant.

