## ***Clinical Implementation Methods***

### **Study Design**

We will use a type III implementation-effectiveness hybrid research design, which allows evaluation of implementation strategy outcomes while observing and gathering information on PSM's impact on relevant clinical outcomes. The five elements of the RE-AIM framework (Reach, Effectiveness, Adoption, Implementation, Maintenance) will be used as an overarching construct for reporting implementation and effectiveness outcomes for this study (Figure 2). The IRBs of all participating sites gave ethical approval for this work.

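### INR control is tested between those who do and do not complete 6 months of PSM, and surveys are analysed in completers only; both select on completion, so neither shows how PSM performs in those who try it

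*Protocol*

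**What the plan says.** The design has no control group: "We will use a type III implementation-effectiveness hybrid research design", and the Abstract states "We aim to implement PSM with 150 adult patients at four sites". Every enrolled participant is meant to try PSM.

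The Reach section fixes the grouping variable: "Successful transition to PSM will be defined as completing 6-months of PSM". Completion is also the numerator of the primary implementation outcome.

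The Effectiveness section then plans three analyses that matter here.

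- A between-group comparison: "INR control outcomes will be compared between eligible participants who do and do not successfully transition to PSM during the 6-month follow-up period". The outcomes are TTR by linear interpolation and the "proportion of INRs resulting in a warfarin dose change". The method is unadjusted: "T-tests and the chi-squared test of association will be used to compare differences in continuous and categorical outcomes between patients who do and do not" reach that definition of success, with two-sided p<0.05 called significant.
- A before-after INR comparison with paired tests: "INR control outcomes will also be compared between the 6-month periods before and after PSM transition attempts". Its wording is not limited to completers.
- A before-after survey comparison that is limited to completers: "For participants who successfully transition to PSM, AKT, ACT, and SF-36 scores will be compared before and after PSM transition".

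**The concern.** Whether a participant belongs to the success group is known only at the end of follow-up, and INR control is measured over that same follow-up. Completion is a post-baseline event that INR control may itself influence. The protocol describes ways this could happen: clinicians remotely review dosing decisions and step in where harm is possible, and participants are told to call the clinic when the INR is extreme or symptoms occur. Someone whose control is poor may therefore be more likely to stop.

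The comparison group is also the wrong one for an effectiveness question. Non-completers are people who tried PSM and did not finish. They are not a group managed by a clinic throughout. A significant t-test placed under Effectiveness invites the reading that PSM improves INR control, when it may show only that people who were doing badly stopped.

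The survey analysis selects on the same event. Knowledge, satisfaction and quality of life are collected at baseline from all consenting participants, but the change is analysed only in those who stayed. The result does not describe everyone who tried PSM.

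**Working it through.** The protocol gives no TTR standard deviation, expected completion rate or effect size behind the 150, so it has no figure of its own to reproduce. The check asks what the planned tests return when PSM has no effect.

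**Inputs from the protocol:** 150 participants, all attempting PSM; groups defined by completion; unpaired t-test between groups; paired t-test for before-after; two-sided 0.05.

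**Assumptions:** TTR before and after has the same mean, SD 20 points and within-patient correlation 0.5. Completion is 60%, 75% or 90%. The log-odds of completion rise by b per SD of the after value, or of the before value, or are unrelated to TTR. A b of 0.25, 0.5 or 1.0 means that the odds of completing multiply by 1.28, 1.65 or 2.72 per 20 TTR points. There were 4,000 simulated trials per setting.

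**1. Completers minus non-completers, follow-up TTR (points; share of trials with p<0.05)**

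| Completion linked to | 60% complete | 75% complete | 90% complete |
|---|---|---|---|
| nothing | 0.0 (5%) | 0.0 (6%) | 0.0 (5%) |
| after value, b=0.25 | 4.9 (32%) | 4.9 (26%) | 4.8 (15%) |
| after value, b=0.5 | 9.4 (82%) | 9.6 (72%) | 9.8 (44%) |
| after value, b=1.0 | 16.6 (>99%) | 17.0 (>99%) | 18.0 (91%) |
| before value, b=0.5 | 4.9 (30%) | 4.7 (24%) | 5.1 (15%) |
| before value, b=1.0 | 8.3 (70%) | 8.5 (61%) | 9.1 (38%) |

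Hand check of one cell. For a modest slope the difference is about b × SD = 0.25 × 20 = 5 points, against 4.9 simulated. At 75% completion the standard error is 20 × √(1/112.5 + 1/37.5) = 3.77, so 4.92/3.77 = 1.31, and P(Z > 1.96 − 1.31) is about 26%, as in the table.

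A second set of assumptions gives the same pattern (SD 12 between and 12 within participants, 25% stopping). If the odds of stopping rise by 22%, 49% or 82% per 10-point lower TTR, completers look 5.6, 10.6 or 14.6 points better, with p<0.05 in about 41%, 93% and over 99% of trials.

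**2. Completers-only before-after change, the structure of the survey analysis (on the same SD 20 scale)**

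- Completion linked to the after value: +0.2 to +3.3 points, p<0.05 in 5% to 35% of trials.
- Completion linked to the before value: −0.5 to −3.3 points, p<0.05 in 6% to 35%. People selected for a high baseline regress towards the mean.
- No link: about 0, with 5% error.

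Hand check. With completion rate c and correlation 0.5, the after-linked change is (1 − 0.5) × (1 − c) × the difference in table 1. For c=0.6 and b=1.0 this is 0.5 × 0.4 × 16.6 = 3.3. The before-linked change is −(1 − c) × the difference = −0.4 × 8.3 = −3.3. Both agree with the simulation.

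**3. Before-after change in all who attempt PSM.** In every scenario the mean change lies between −0.07 and +0.08 points, with an error rate of 4.3% to 5.7%. This analysis is free of the selection problem.

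**The case against.** The best reply is that the protocol never calls the completer contrast a PSM effect. This is a type III hybrid whose primary outcome is the percentage who transition, clinical outcomes are observed alongside, and no decision or sample size rests on this test. Reach records when and why people stop and compares baseline characteristics by success, which helps a reader interpret the contrast. All of that stands. It lowers the severity, but it does not make a significance test listed under Effectiveness interpretable as effectiveness.

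A reader might infer that both analyses favour PSM whatever the truth. The documents do not support that. There is no INR-based rule for PSM failure and no stated link between stopping and control; without a link the contrast is centred on 0 with about 5% error. For the surveys even the sign is open. Upward bias is the more plausible direction, if dissatisfied participants stop, but regression to the mean can pull the other way.

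A reader might also infer that the protocol has no sound INR comparison. It does: the before-after comparison is framed around transition attempts and not completion.

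Two further points for the defence stand. Collection of the final survey is not clearly restricted, since the text and Table 3 do not limit it to completers; only the analysis set is. How post-stopping INRs enter TTR, and how many INRs interpolation needs, may properly be settled in a statistical analysis plan that is not shown, so their absence is not part of this point.

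**Conclusion.** The point holds in a limited form. The INR contrast and the survey analysis both condition on completing 6 months of PSM. For the INR contrast this rules out an effectiveness reading in either direction, because both groups attempted PSM. That conclusion needs no assumption.

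The size does need assumptions. If completion is related to INR control, before or after transition, the spurious advantage to completers is about 5 to 18 TTR points, with a false positive in 15% to over 99% of trials. The SD, correlation, completion rates and strength of link behind those figures are not in the protocol. For the surveys the bias is smaller on the same scale, up to about 3.3 points, and its direction is unknown.

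This should be fixed, because it concerns how effectiveness results will be read. It does not affect the primary implementation outcome, and the contrast need not be deleted.

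**What to change.** 1. Report TTR and dose-change frequency by completion status as a description of who succeeds, without a significance test presented as effectiveness.
2. State that the before-after INR comparison already planned includes everyone who attempts PSM, whether or not they complete, using INRs from the EHR for the rest of the 6 months after stopping. Name it as the effectiveness analysis of INR control, and acknowledge that it has no concurrent control.
3. State that the final survey also goes to participants who stop. Analyse everyone with a baseline survey, with a stated approach to missing responses, and keep completers only as a supplementary analysis.

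The cost is a change of wording, INR extraction for participants who stop, and one extra emailed survey for them. Some will not respond, so the survey analysis will still depend on assumptions about missing data, but these will be explicit.

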## Patient selection criteria

General PSM patient selection criteria will include 1) medical stability at the time of PSM initiation; 2) cognitive stability and capable of following instructions and/or has a willing and capable caregiver; and 3) currently self-testing with a home INR device. Specific PSM patient selection criteria related to participation in the PSM implementation study will include 1) goal INR range of 2.0 to 3.0 or 2.5 to 3.5; 2) completed more than 9 months of warfarin therapy at time of enrollment; 3) willing to use single warfarin tablet strength; 4) planned duration of warfarin therapy of at least 6 months; 5) willing to test INR every 7-14 days; 6) receiving majority of care within the enrolling site's healthcare system; and 7) able to maintain internet access throughout study participation.

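### The before/after McNemar test for bleeding and thromboembolic events is not like for like, because entry conditions remove some events from the 'before' window

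*Protocol*

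**What the plan says.** The Effectiveness section of the Protocol fixes the comparison: "Additional effectiveness outcome comparisons before and after PSM transition will include major bleeding and clinically relevant non-major bleeding events". The same sentence adds "thromboembolic events, and all-cause mortality". The test is named: "Paired t-tests and McNemar's test will be used to compare differences between continuous and categorical outcomes before and after PSM transition, respectively". So is the threshold: "Two-sided P-values <0.05 will be considered statistically significant". The window length is stated for INR control ("INR control outcomes will also be compared between the 6-month periods before and after PSM transition attempts"), and I take it to apply to events as well.

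The Patient selection criteria require "medical stability at the time of PSM initiation", "completed more than 9 months of warfarin therapy at time of enrollment" and "planned duration of warfarin therapy of at least 6 months", as well as current home INR testing. No definition of stability and no look-back period is given. Under Recruitment process, clinicians record their confidence in the patient and whether they recommend inclusion. Under PSM implementation phase, they decide again whether a participant should move on to the supervised dosing phase.

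The design is a single group with a planned enrolment of 150 and no concurrent control.

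**The concern.** McNemar's null hypothesis is that the chance of an event is the same in the two paired periods. Here the two chances differ by selection even if PSM does nothing, because the patients are chosen by their state at the end of the first period. Someone whose bleed or clot was fatal, ended warfarin or left them unstable at the time of entry never contributes a 'before' event. The same event after transition is counted, provided that everyone who attempts PSM is analysed.

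The Discussion says that the study will inform whether US patients can do PSM safely. With no control group, the patients' own 'before' period is the only reference for event rates. A depleted reference could produce an apparent excess of bleeding or clotting, or hide a real reduction.

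**Working it through.** **From the Protocol:** 150 participants; two windows, taken as 6 months each; McNemar's test; two-sided 0.05. There is no planned event rate or effect size, so no figure in the plan can be reproduced.

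**Assumptions:** true 6-month risk p, equal in both windows (no PSM effect); a share f of 'before' events removed by the entry conditions; the two periods independent within a patient; all 150 analysed; McNemar without continuity correction, since the Protocol does not name a version.

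**What makes up f.** Let d be the share of events that are fatal or end warfarin (missing from all 6 months). Let u be the share that leave the patient unstable for s months (missing from the last s months only). Then f = d + u × s/6.
- d=0, u=1/4, s=2: f = 0.25 × 2/6 = 1/12. Taking d=1/12 and u=0 gives the same value.
- d=0, u=1/2, s=2: f = 0.5 × 2/6 = 1/6.
- d=0, u=1, s=3: f = 3/6 = 1/2. Here every event of the last 3 months disqualifies, which is a worst case.

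**Bias in the estimate.** The observable 'before' risk is (1-f)p and the 'after' risk is p, so the apparent ratio is p/[(1-f)p] = 1/(1-f). This gives 1/(11/12) = 1.09, 1/(5/6) = 1.20 and 1/(1/2) = 2.00.

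**Effect on the test.** The discordant-pair probabilities are:
- after only: p × [1-(1-f)p]
- before only: (1-f)p × (1-p)

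For p=10% and f=1/6 these are 0.10 × 0.9167 = 0.0917 and 0.0833 × 0.90 = 0.0750. About 150 × 0.1667 = 25 discordant pairs are expected, and 55% of them point to harm instead of 50%. Summing exactly over the number of discordant pairs gives the chance of a significant result in the harm direction:

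| f | ratio | p=1% | p=5% | p=10% |
|---|---|---|---|---|
| 0 | 1.00 | 1.5% | 2.3% | 2.6% |
| 1/12 | 1.09 | 1.7% | 3.3% | 4.5% |
| 1/6 | 1.20 | 1.9% | 4.8% | 7.5% |
| 1/2 | 2.00 | 3.1% | 18.5% | 38.6% |

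The exact version of McNemar's test is more conservative. At p=5% it gives 1.3%, 2.0%, 2.9% and 12.5% down the column.

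**If only 6-month completers are analysed.** A share g of 'after' events is then also lost, and the ratio becomes (1-g)/(1-f). With f=1/6 it is 1.20 at g=0, 1.00 at g=1/6 and 0.80 at g=1/3.

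**The case against.** The strongest objection is about size. Nothing in the selection criteria says that a clinically relevant non-major bleed disqualifies a patient. Stability is judged at initiation, with no look-back, and a clot may lead to continued warfarin. Many 'before' events therefore remain countable, and treating every event of the last 1 to 3 months as excluded overstates the effect. This stands: the f=1/2 row is a worst case, and the f=1/12 row shows how small the effect may be.

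The 5% and 10% risks are also assumptions. The Protocol lists major bleeding, non-major bleeding and thromboembolism without defining a composite. For a single outcome with a 1% risk, the false-harm rate stays at or below 3.1%. This stands too: for rare events the bias lies in the estimate, not in the p-value.

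The direction can also be questioned. Success is defined as completing 6 months of PSM. If 'after' events were counted only in completers, participants who failed because of an event would drop out of that window. The restriction to successful participants is written only for the knowledge, satisfaction and quality-of-life scores, so analysing all who attempt PSM is the more natural reading. It is not stated for events, however.

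Finally, the primary outcome is implementation, these comparisons are secondary, and caveats are often left to an SAP. That lowers the stakes. But the Protocol itself names the contrast, the test and the threshold, so following it as written yields the biased comparison.

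**Conclusion.** The point holds as a partial and asymmetric depletion of the 'before' window. If all who attempt PSM are analysed, the after/before ratio is biased upwards by 1/(1-f) for any f above 0. Under the assumptions above, that means a ratio of 1.09 with a false-harm rate of 3.3% to 4.5% (f=1/12), and 1.20 with 4.8% to 7.5% (f=1/6). The worst case (f=1/2) gives 2.0 with 18% to 39%. Neither f nor the event rate can be taken from the Protocol, so no single size can be claimed.

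A reader might infer that PSM is bound to look harmful, or that a false safety signal is likely. The documents do not support this. Depletion is only partial, its extent is unknown, and under a completers-only analysis the bias could cancel or reverse. What holds on either reading is that the two windows are filtered differently, so the McNemar p-value for these events does not isolate an effect of PSM.

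**What to change.** In the Effectiveness section of the Protocol:
1. Remove bleeding and thromboembolic events from the before/after McNemar comparison.
2. Report post-transition events per patient-year with exact 95% confidence intervals as the safety result, and state that the population is all participants who attempt PSM.
3. Give 'before' counts descriptively, with a sentence saying that the entry conditions deplete them.

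I would not try to rescue the test by counting, in both windows, only events after which the patient was alive, on warfarin and stable. That would discard the most serious events under PSM, and it needs a stability judgement at the end of follow-up that Table 3 does not list.

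The cost is a wording change and a simple rate analysis, using event chart reviews that Table 3 already schedules before and after the study. The before/after p-value for clinical events is given up.
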